## Abstract

**Background:**

Obstructive sleep apnea occurs as a result of increased collapsibility of the upper airway. Overnight fluid displacement from the legs to the neck causes pharyngeal narrowing and increased apnea severity. Sodium intake is associated with apnea severity. We hypothesized that interventions that decrease bodily fluid content might reduce the severity of sleep apnea.

**Methods/design:**

This is a randomized clinical trial including men with an apnea-hypopnea index greater than 30 events/hour, previously diagnosed by full-night in-laboratory polysomnography. A total of 54 men will be included and randomly assigned to three groups: Diuretic (*n* = 18), sodium-restricted diet (*n* = 18), and control (*n* = 18). The intervention will last one week. Intention-to-treat and per-protocol analyses will be performed. The diuretic group will receive combined spironolactone 100 mg plus furosemide 20 mg daily, taken in the morning. The diet group will receive a regimen with a maximum intake of 3 g of sodium per day. The control group will receive a placebo pill and will maintain all eating habits while keeping a recall diary of their dietary behavior. The primary outcome measure will be change in apnea-hypopnea index. The secondary outcome measures will be variations of: anthropometric and bioelectrical impedance variables, office blood pressure, respiratory variables from in-home level III polysomnography, excessive daytime sleepiness, glycolipid profile, C-reactive protein, 24 h urinary variables, and adverse events.

**Discussion:**

Despite the high efficacy of continuous positive airway pressure to reverse upper airway obstruction in sleep apnea, partial adherence to this form of treatment reduces its efficiency. Thus, additional forms of treating apnea need to be investigated. If the results of this proof-of-concept trial show that decreases in bodily fluid content, either by diuretic or dietary intervention, reduces the severity of sleep apnea, further investigation will be necessary before these results can be translated and adopted as an adjunct apnea therapy.

**Trial registration:**

clinicaltrials.gov NCT01945801.

## Background

Obstructive sleep apnea is a disorder characterized by repetitive collapse of the upper airway during sleep [1]. Its prevalence is increasing [2], reaching, in one study, 32% of the general adult population [3]. One reason for this growing prevalence of sleep apnea is the obesity epidemic, since obesity and neck circumference are risk factors for apnea. Sleep apnea, however, is also observed in non-obese people. In large samples, half of patients with apnea have body mass indexes below 27.6 kg/m^2^ [4].

Rostral fluid shift, that is, a shift of fluid from the lower to the upper body, produces a significant increase in neck circumference, pharyngeal resistance, and upper airway collapsibility [5-10]. Wearing elastic stockings during the day reduces the apnea-hypopnea index by more than one-third in sedentary individuals [11] and in patients with venous insufficiency [12]. Preventing fluid retention might reduce overnight fluid shift from the legs to the neck.

Diuretics given to patients with uncontrolled hypertension reduced their apnea-hypopnea index by 16%, an effect size of 0.3 [13]. In resistant hypertension, spironolactone reduced patients’ apnea-hypopnea index by approximately 50%, an effect size of 1.2 [14]. Also, diuretics improve sleep-disordered breathing and increase pharyngeal caliber in patients with severe obstructive sleep apnea and diastolic heart failure [15].

Fluid retention is proportional to sodium intake. Patients with sleep apnea have significantly greater sodium intake than patients without. In receiver operating characteristic (ROC) curve analysis, a sodium intake above a cutoff value of 2.4 g/day predicted moderate to severe sleep apnea (area under the ROC curve of 0.78) [16].

The upper limit of recommended sodium intake for healthy adults is 2.3 g/day [17]. Bibbins-Domingo et al. project that a reduction of dietary salt could halve the annual number of new cases of coronary heart disease, stroke, and myocardial infarction, and the number of deaths from any cause in the United States [18]. It is possible that part of the projected effect of salt restriction may be due to the effect of fluid retention on obstructive sleep apnea severity.

Continuous positive airway pressure (CPAP) is highly efficacious in treating obstructive sleep apnea. Many patients, however, find it difficult to tolerate its use. Poor adherence to CPAP treatment leads to reduced control of associated morbidities [19]. Reductions in blood pressure levels are seen only when CPAP use is above 5.6 hours per night [20]. Alternatives to CPAP treatment have problems of incomplete efficacy and adherence. Mandibular advancement oral appliances are similar to CPAP in controlling hypertension [21]. Various surgical approaches have diverse results [22].

Therapy of sleep apnea, therefore, is not a settled issue. Broadening comprehension of the pathogenesis of obstructive sleep apnea may help in the search for new and better tolerated treatments for the millions of people with sleep apnea.

We hypothesized that in the usual patient with apnea, without such conditions causing fluid retention as heart, renal, or venous failure, decreasing fluid retention using diuretics and a sodium-restricted diet might change sleep apnea severity. To test this hypothesis, we will conduct a trial in which the primary outcome measure is the apnea-hypopnea index. The secondary outcome measures are anthropometric and bioelectrical impedance variables, blood pressure, respiratory variables in-home polysomnography, excessive daytime sleepiness, glycolipid profile, C-reactive protein, 24 h urinary variables, and adverse events.

### Rationale

Apnea severity has been associated with overnight fluid displacement from the legs to the neck. Peripharyngeal fluid accumulation predisposes patients to upper airway collapse. Diuretics or a sodium-restricted diet offer therapeutic potential for sleep apnea by preventing fluid retention.

### Research question

Is a diuretic or a sodium-restricted diet capable of reducing the apnea-hypopnea index in comparison with a control group?

## Methods/design

### Study design

This study is a parallel randomized, blind, placebo-controlled superiority trial.

#### Eligible participants

*Inclusion criteria*Men aged from 18 to 60 years;Full-night in-laboratory polysomnography with apnea-hypopnea index greater than 30 per hour in the past three months;Body mass index less than 35 kg/m^2^;Informed consent.

*Exclusion criteria*Already receiving treatment for sleep apnea, including CPAP;Heart failure, any New York Heart Association class;More than 50% of the apnea events being of central origin;Any chronic renal disease;Peripheral venous or lymphatic insufficiency;Use of diuretics and substances with action on the central or peripheral nervous system, such as benzodiazepines, hypnotics, anticonvulsants, antidepressants, appetite suppressants, amphetamines, antiparkinson agents, muscle relaxants, bronchodilators;Stroke within the past 6 months or with incapacitating sequelae;Any physical, mental, or social condition impairing the ability to participate in the trial.

### Sample size

Sample size calculations were performed for repeated measures analysis of variance using G*Power software 3.1.9.2 [23]. Hypothesizing an effect size of 0.25 for a power of 90% at *P* alpha < 0.05, for three groups, a sample size of at least 18 in each arm of the study was required, totaling 54 individuals. In case of loss to follow-up, extra volunteers will be enrolled to compensate. Losses will be included in the intention-to-treat but not in the per-protocol analyses.

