### Statistical methods

Outcomes will be analyzed by intention-to-treat and per-protocol. A low attrition rate is expected, since the interventions are of short duration and minimal risk. Missing data will be considered as missing. Data imputation will not be employed.

Normally distributed data will be presented as means and standard deviation. Non-normally distributed data will be displayed as median and interquartile range. Natural logarithm transformation of the apnea-hypopnea index in events/h will be employed to correct its non-normal distribution in analyses that assume normal data distribution. The significance of the differences between intervention groups will be tested by chi-squared test for categorical variables and generalized estimating equations method, followed by pairwise comparisons with the sequential Bonferroni correction for continuous variables. Logistic and linear regression models will be used to adjust results for age and body mass index. Results with a *P* value lower than 0.05 for alpha error will be considered statistically significant. Statistical analyses will be performed using SPSS software (SPSS Inc., Chicago, IL, USA).

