### Follow-up and duration of the study

There will be two visits at the clinical research center, one before (baseline) and one after (follow-up) the one-week pill plus diet intervention.

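### Men lost to follow-up are counted in the intention-to-treat analysis but can supply only a baseline AHI; the resulting bias is conditional and small, and adjusting for baseline removes the part related to baseline severity at almost no cost

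*Protocol article*

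**What the plan says.** Four statements in the protocol article bear on this point.

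- Sample size: "In case of loss to follow-up, extra volunteers will be enrolled to compensate", followed by "Losses will be included in the intention-to-treat but not in the per-protocol analyses".
- Statistical methods: "Missing data will be considered as missing. Data imputation will not be employed". The same paragraph adds "A low attrition rate is expected, since the interventions are of short duration and minimal risk", without a figure.
- Statistical methods: continuous variables are compared by "generalized estimating equations method, followed by pairwise comparisons with the sequential Bonferroni correction for continuous variables", with AHI log-transformed where normality is assumed. No working correlation is named. The only covariates listed for adjustment are age and body mass index.
- Follow-up and duration of the study: "There will be two visits at the clinical research center", one before and one after the treatment week. Assessment of outcomes (sleep respiratory variables) places the AHI recordings at the baseline and follow-up nights only.

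The abstract defines the primary outcome as the change in AHI.

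**The concern.** A man who is lost has no post-treatment AHI, no intermediate value and no imputed value, so he has no change. Counting him in the intention-to-treat set adds at most his baseline to the GEE.

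Under an independence working correlation, the estimated change in an arm is the follow-up mean of the men who returned minus the baseline mean of all men in the arm. The two means describe different sets of men. If those who leave tend to have a high baseline AHI, the arm appears to improve when nobody has changed. If change scores are analysed instead, the lost men drop out altogether and regression to the mean pushes the error the other way. The intention-to-treat label gives the reader no warning of either effect.

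**Working it through.** **Inputs.** From the document: 18 men per arm, three arms, effect size 0.25, power 90%, alpha 0.05 (Sample size); two visits; no imputation; GEE. Assumed, because the document gives no figure: correlation ρ = 0.5 between visits, equal variance at both visits, and the number and pattern of losses. Results are in SD units of the analysed (log) AHI. A negative sign favours the arm with losses.

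**1. The plan's own figure.** For the arm-by-time interaction with N = 54 and m = 2 visits, λ = f²·N·m/(1−ρ) = 0.0625 × 54 × 2/0.5 = 13.5 on 2 and 51 degrees of freedom. Power is 0.902, so the stated size reproduces and is not in dispute.

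This also fixes the scale of the planned effect. The variance of a change is 2(1−ρ) = 1, so the SD of the arm mean changes is √(13.5/54) = 0.5. The largest difference between two arms is then 0.5 × √4.5 = 1.06 SD (one arm against two equal ones) to 0.5 × √6 = 1.22 SD (evenly spaced arms).

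**2. Bias formula.** Let D be the baseline mean of the men who returned minus the baseline mean of all men in the arm. With no true effect and loss related only to baseline:

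- GEE, independence: ρ·D
- Completers' change: −(1−ρ)·D
- GEE that uses the correlation, or ANCOVA on baseline: about 0

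**3. Numbers.** In a normal sample of 18, the six highest values average about 1.04 SD. Losing k of those six gives D = −1.04·k/(18−k).

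- k = 1: D = −1.04/17 = −0.061, so independence GEE −0.03 and completers' change +0.03.
- k = 3: D = −1.04 × 3/15 = −0.208, so independence GEE −0.10 and completers' change +0.10.

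Simulation (40,000 trials, 18 per arm, losses in one arm only) agrees:

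| Men lost, and how | GEE, independence | GEE using ρ | Completers' change | ANCOVA |
|---|---|---|---|---|
| 1 from the most severe third | −0.03 | 0.00 | +0.03 | 0.00 |
| 3 from the most severe third | −0.106 | 0.00 | +0.103 | −0.001 |
| 3 at random, one arm only | 0.00 | 0.00 | 0.00 | 0.00 |
| 3 from the third whose AHI rose most | −0.10 | −0.16 | −0.21 | −0.16 |

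**4. By attrition rate.** In a large-sample check with loss only among men above the median baseline, independence GEE gave −0.02 at 5% loss, −0.04 at 10% and −0.10 at 20%.

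**5. Replacement.** Suppose the three lost men are replaced by three average men who complete, and the lost men stay in the intention-to-treat set. Then D = −1.04 × 3/18 = −0.173 and the independence bias is 0.5 × −0.173 = −0.09. Replacement restores the number with follow-up data but removes little of the bias.

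**6. Precision.** The standard error of a between-arm difference in change is √(2 × 2(1−ρ)/18) = 0.333. With baseline adjustment it is √(2(1−ρ²)/18) = 0.289. In simulation, which includes the cost of estimating the slope, the figures are 0.337 and 0.297. Since 0.297/0.337 = 0.88, the reduction is about 12%. A GEE with separate baseline means per arm does not gain this, even when its working correlation is right.

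**The case against.** **Working correlation.** The independence structure is an assumption. The article names none and may properly leave the choice to a fuller document, so its absence is not a fault. Under a structure that uses the correlation, the baseline-dependent bias goes to about zero and the lost men's baselines do useful work. This stands, and it makes the bias conditional.

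**Loss by arm.** A reader might infer that heavier loss in the diuretic or diet arm is enough to bias the result. It is not. Arm is in the model, so loss that is random within an arm leaves each arm's means intact, as the third row of the table shows. Loss must be related to AHI within the arm.

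**Size.** A reader might set 0.11 SD against the effect size of 0.3 quoted in the Background and call it a third of the effect. That figure comes from one earlier study in uncontrolled hypertension, and the Background also quotes 1.2. Against the effect this trial is sized for, 0.11 SD is about a tenth (0.11/1.06 = 0.10), and about a third of one standard error (0.11/0.333 = 0.33). It also needs three losses from 18, all from the most severe third of one arm, while the protocol expects low attrition over one week.

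**Whether intention-to-treat is empty.** A reader might conclude that the promise cannot be kept at all. A two-visit GEE does retain every man who has a baseline, and available-data analysis without imputation is openly stated. The wording is loose, not void. It would be empty only if change scores were analysed.

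**Remedy.** ANCOVA and mixed models are no safer under outcome-dependent loss. That is true (about −0.16 SD with three lost), so they need a sensitivity analysis beside them.

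**Conclusion.** The point holds in a limited form. Read together, the rules mean that a lost man contributes a baseline and no change, and the sentence on losses does not say so. The intention-to-treat estimate is biased by baseline-dependent loss only if two conditions meet: loss within an arm is related to baseline severity, and the GEE uses independence. At ρ = 0.5 the bias is then about −0.03 SD with one man lost and −0.11 SD with three. The loss counts, the mechanism and ρ are all assumed. The documents do not support saying that the planned result is biased, only that the stated rules leave it open to bias.

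The expected harm is modest. The change is still worth making: adjusting for baseline protects against this loss pattern without depending on the working correlation, and it improves precision whether or not anyone is lost.

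**What to change.** 1. State that all randomised men are analysed as assigned on log AHI, with the primary comparison adjusted for baseline log AHI. Use either ANCOVA or a two-visit likelihood model with unstructured covariance and a common baseline mean across arms.
2. Reword the sentence on losses under Sample size: men without a follow-up recording contribute baseline data only. Under the two-visit model that baseline enters the fit; under ANCOVA it does not affect the estimate, and the text should say so.
3. Add one sensitivity analysis for outcome-dependent loss. A simple form shifts each arm's estimated mean from the two-visit model by the fraction lost times an assumed difference δ between lost and similar retained men, over a range of δ. With 3 of 18 lost and δ = 1 SD, the shift is 3/18 × 1 = 0.17 SD. This needs no imputed records, so it fits the rule that "Data imputation will not be employed".

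The cost is analysis wording and one extra run. No visit, measurement or sample size changes.

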#### Randomization process

Randomly permuted blocks of six numbers, obtained from randomization.com [24], will be employed. Patients will be assigned to one of the three groups by a researcher not otherwise involved in the protocol.

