### Blinding

The researchers taking measurements for either primary or secondary outcome measures, as described herein, will be blind to the group assignment. On completion of the study, volunteers will be asked to which group they believe they were assigned, to allow assessment of the blinding success [25].

The nutritionist, who delivers the diets, the only non-blinded intervention, will not be aware of the pills supplied to the unmodified diet groups and will not be involved in other steps of the protocol. The scoring of the apnea-hypopnea index will be performed remotely via the internet by a third-party certified scorer. The blinding code will be broken at the end of the study or earlier by request of regulatory committees or in the case of adverse events in connection with the group assignment.

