## Trial status

At the time of manuscript submission, the enrollment of volunteers is ongoing.

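### One fixed, disclosed block size of six alongside an open diet arm can make diet or not-diet status certain in advance for up to about 16 of 54 men, if recruiting staff learn who received the diet

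*Protocol article*

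**What the plan says.** The protocol article fixes the allocation method under Randomization process: "Randomly permuted blocks of six numbers, obtained from randomization.com [24], will be employed". It names no other block size and no stratification. The same section adds: "Patients will be assigned to one of the three groups by a researcher not otherwise involved in the protocol". The abstract gives three arms of 18, so 54 men.

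Under Blinding, the open arm appears in a sentence that also sets limits on the person delivering it: "The nutritionist, who delivers the diets, the only non-blinded intervention, will not be aware of the pills supplied to the unmodified diet groups", and this person "will not be involved in other steps of the protocol". The same section keeps those who measure outcomes blind to group and has the apnea-hypopnea index scored remotely by a third party. The section on interventions makes active and placebo pills and flasks identical.

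Under Recruitment, men are picked from a laboratory list and telephoned. The intervention week starts only once the volunteer has confirmed that it is free of social commitments. The article does not say who makes these contacts, or whether that person learns earlier diet assignments. Trial status reads: "At the time of manuscript submission, the enrollment of volunteers is ongoing".

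**The concern.** A fixed block size is harmless when nobody near enrolment can see past assignments. Here one arm in three is open by design. Once both diet places in a block are taken, every remaining man in it must be on a pill. If the diet places left equal the men left, all of them must be on the diet. The independent assigner protects the list, but this deduction does not need the list. It needs only the block size and the earlier diet assignments.

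Entry leaves some room for discretion: the order of telephone calls, the choice of week, and an exclusion criterion that turns on a judgement of whether a man is able to take part. Someone who foresees a diet place could defer a man thought unlikely to keep to a strict diet. With 18 men per arm, steering a few could distort a comparison with the diet arm. The planned adjustment for age and body mass index would not capture motivation or likely adherence.

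**Working it through.** **Inputs.** Block size 6 (Randomization process). Three arms of 18, total 54 (abstract). Two men per arm per block is inferred from the equal arms: 6/3 = 2. Number of blocks: 54/6 = 9. The article gives no figure for predictability, so there is none to reproduce.

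**Assumption.** The observer knows the block size and sees every earlier diet assignment, and men are assigned one after another from a single list.

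**Certain allocations, fixed blocks of six.** The two diet places can fall in C(6,2) = 15 equally likely ways. A man's status is certain before assignment when all remaining places are of one kind: either both diet places are already used, or the diet places left equal the places left.

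| Position in block | Both diet places already used | All remaining places diet | Certain |
|---|---|---|---|
| 1 | 0 | 0 | 0/15 = 0% |
| 2 | 0 | 0 | 0/15 = 0% |
| 3 | C(2,2) = 1 | 0 | 1/15 = 6.7% |
| 4 | C(3,2) = 3 | 0 | 3/15 = 20% |
| 5 | C(4,2) = 6 | 1 | 7/15 = 46.7% |
| 6 | C(5,2) = 10 | 5 | 15/15 = 100% |

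The sum is 26/15 = 1.73 men per block. As a share this is 1.73/6 = 28.9%. Over nine blocks it is 9 × 26/15 = 15.6 men of 54. The sixth position alone contributes 1.00 of the 1.73.

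**Best-guess accuracy, fixed blocks of six.** At each position the observer guesses the more likely status. The mean chance of being right, by position, is 66.7, 66.7, 66.7, 73.3, 73.3 and 100%. The average is 74.4%. Always guessing not-diet is right 4/6 = 66.7% of the time.

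**Diuretic versus control.** If a man is known not to be on the diet and nothing else is known, the chance of diuretic is 2/4 = 50%. Block size and diet visibility do not move this.

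**Varying block sizes.** Sequences of 54 were simulated with sizes drawn at random with equal chance. The observer knows the possible sizes but not the current one, and updates by Bayes' rule. As a check, fixed six in this simulation gives 28.8% certain and 74.3% best guess, matching the exact values. The ranges come from two separate simulation runs.

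| Scheme | Certain in advance | Best-guess accuracy |
|---|---|---|
| Fixed 6 (exact) | 28.9% (15.6 of 54) | 74.4% |
| 3, 6, 9 | about 3.7 to 4% (about 2 of 54) | about 73.4 to 73.6% |
| 6, 9, 12 | about 2.3 to 2.5% (about 1 of 54) | about 71.6 to 71.7% |

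The mix without blocks of three does better on both measures.

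**The case against.** The strongest reply is that the article separates the people who know. The assigner is uninvolved in the rest of the protocol, the nutritionist takes no part in other steps, and outcome assessors and the remote scorer are blind. No one documented as knowing who received the diet is documented as recruiting. Concealment detail of that kind is commonly left to a full protocol. This stands, and it makes the risk conditional. It does not remove the point, because the fixed block size is a choice the article states, and varying it protects whatever the recruiting staff happen to know.

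It is also fair that 28.9% is a worst case, that more than half of it is the last man in each block, and that varying the sizes lowers best-guess accuracy by only one to three percentage points. The gain lies mainly in removing certainty. The steering route is inferred too: the volunteer confirms the week, and the article does not say whether this comes before or after assignment.

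A reader might go further and infer that the blind between diuretic and placebo unravels. The documents do not support that. The pills are identical, and seeing the diet men leaves the others at 50:50. A further leak would be needed. After one code break, each of the other three pill men in that block has a 2/3 chance of being in the opposite arm. Identifying all of them would take two breaks in the same arm of one block, with both diet men also known. The article allows early unblinding "in the case of adverse events in connection with the group assignment", but it does not say the result reaches the assessors or the scorer. Silence on who receives it is ordinary brevity in an article.

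Nor does the article show that the block size was public while men were still being enrolled. It reports enrolment as ongoing at submission, not at publication.

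**Conclusion.** The point holds in a conditional form. A single disclosed block size of six, with one open arm of three, makes diet or not-diet status certain in advance for up to 28.9% of allocations (about 16 of 54). This assumes two men per arm per block, and recruiting or scheduling staff who know the block size and learn all earlier diet assignments. The article neither states nor excludes that knowledge. With partial knowledge the share is smaller, and with none the problem does not arise.

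What is exposed is selection into the diet arm, and so the comparisons that involve it. The diuretic-control comparison is not revealed by this mechanism, and the sample size is unaffected. Fixed permuted blocks are not an error in themselves, but in this design they are an avoidable weakness that is cheap to repair.

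**What to change.** For men not yet randomized, generate a new list with randomly varying block sizes in multiples of three, preferably without blocks of three, for example 6, 9 and 12. The independent assigning researcher should hold it, and the sizes should not be disclosed to anyone who recruits or schedules men. Starting it at the end of a block of six keeps the arms level at the switch.

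The cost is a new list, a recorded change to the conduct of a running trial, and a possible small imbalance in final arm sizes. If enrolment stops inside a block of 12, two arms can differ by at most 12/3 = 4 men. The change helps only while men remain to be randomized.
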